#### Qualitative component.

The qualitative component will employ convenient sampling and include 10 In-Depth Interviews (IDIs) (one male and one female participant from each of the five study blocks), 5 Focus Group Discussions (FGDs) (one per block), and 12 Key Informant Interviews (KIIs) involving ASHAs, Mukhiyas, NGO representatives, traditional healers, Medical Officers, and other key stakeholders. The proposed methods and sample distribution are presented in Table 1. The proposed sample size is based on the principle of thematic saturation and is expected to provide adequate representation across gender, age, and stakeholder groups. Data collection will continue until thematic saturation is achieved; however, if new themes emerge, additional interviews (up to 20% of the proposed sample) may be conducted after notification to the Institutional Ethics Committee (IEC). Data collection will continue until thematic saturation is reached.

**Table 1 pone.0358356.t001:** Qualitative data collection methods and sample distribution.

Method	Convenient Sampling	Total
IDIs	2(Male, Female from each block)	10
FGDs	1 per block	5
KIIs	(ASHA, Mukhiya, NGO’S, local leader, Traditional Healers, Medical Officers)	12

### Sampling strategy

#### Quantitative component.

A multistage stratified random sampling strategy will be employed for the quantitative component. In the first stage, five tribal-dominated blocks of East Singhbhum district (Golmuri–Jugsalai, Potka, Ghatshila, Dhalbhumgarh, and Ghurabandha) will be included. In the second stage, five villages will be randomly selected from each block, resulting in a total of 25 study villages. The distribution of the sample across the five blocks and 25 selected villages is illustrated in Fig 2. Finally, eligible participants aged ≥45 years will be selected using proportionate allocation and systematic random sampling within each selected village until the required sample size is achieved Table 2–5.

**Fig 2 pone.0358356.g002:**
[figure not shown]
Representing sample size distribution in 5 blocks and 25 villages respectively.

**Table 2 pone.0358356.t002:** Depicting Operational Framework for Replication of Healthcare.This model ensures sustainability by fostering community ownership through tribal leaders, village councils and tribal volunteers, moving beyond disease-centric care to a holistic approach that tracks autonomy and quality of life.

S.No.	Intervention Pillar	Key Strategies	Replicability Features
1.	Outreach	Monthly mobile clinics & AYUSH integrated geriatric-NCD screening.	SOP-driven screening; fixed calendar communicated via Sahiyas.
2.	Digital	Elderly Day with teleconsultations for remote access to specialists.	Digital attendance logs; CHO-managed video/audio sessions.
3.	Entitlement	Convergent enrollment in Ayushman Bharat & pension schemes.	Household entitlement checklists; inter-sectoral coordination.
4.	Capacity	ToT Model for Sahiyas, Healthcare workers and community volunteers in functional care.	Cascade training protocols; 6-month refresher training.
5.	Traditional	Validation of tribal healing practices by AYUSH doctors.	Standardized safety & validation checklists for healers.
6.	Nutrition	Training on MNA tools, kitchen gardens, and tribal diet promotion.	Alignment with Poshan Abhiyan; local agricultural synergy.
7.	Psychosocial	Block-level support groups & home-based physical/mental/social rehab.	Facilitator guides for SHG-linked elderly support groups.

**Table 3 pone.0358356.t003:** Core components of the proposed community-based integrated healthcare model.

Category	Key Details & Strategies	Unique Features / Strategic Role
**Contextual Assessment**	**Strengths:** Close-knit community networks, reliance on traditional healing, and indigenous knowledge systems. **Weaknesses:** Limited formal infrastructure, staff shortages, low literacy, and economic vulnerability.	**Strategic Role:** These insights guide the tailoring of interventions, ensuring the model builds on community strengths while addressing critical gaps.
**Approach to Healthcare**	**Community-Based:** Delivered through health workers, mobile units, and local organizations. **Orientation:** Preventive and promotive (early screening, health education, lifestyle modification).	**Holistic Approach:** Focuses on combining physical, mental, and social well-being rather than exclusively focusing on disease management.
**Healthcare Delivery System**	**Primary:** ASHAs, ANMs, and volunteers for screening and home visits. **Secondary:** CHCs/District Hospitals with dedicated geriatric/NCD clinics. **Tertiary:** Referral links to medical colleges.	Establishes a **structured referral and monitoring pathway** customized for the tribal landscape.
**Integration with Existing Programs**	Leverages **NPHCE, NPCDCS, NHM**, and national nutrition programs such as **ICDS and Poshan Abhiyan**.	**Unique Feature:** Provides programmatic convergence customized for tribal/elderly needs, which is rarely done systematically in existing models.
**Traditional Healing Practices**	Recognizes and documents traditional healers; promotes safe, evidence-based practices while discouraging harmful ones.	**Unique Feature:** Structured collaborative engagement with traditional healers to improve the community’s trust and acceptability of modern healthcare.
**Nutritional Practices**	Incorporates **tribal diets** and local food diversity; introduces low-cost, culturally acceptable interventions like kitchen gardens.	**Unique Feature:** Blends nutrition security directly with healthcare delivery rather than treating them as separate entities.
**Elderly-Focused Interventions**	Builds on NPHCE but is adapted for tribal settings, including **functional decline (ADL/IADL)** and quality of life assessments	**Unique Feature:** Adds community-based care models that specifically account for caregiver burden, social isolation, and financial dependence.

**Table 4 pone.0358356.t004:** Representing outcome measures and assessment timeline.

S.No.	Timeline	Outcome Components	Measurement Tools & Methods
1.	Phase1: Needs Assessment (Completion by November 2026	Baseline Functional Status, QoL, and Morbidity	• Barthel’s Index (for ADL) and Lawton’s Scale (for IADL). • WHOQOL-BREF questionnaire for Quality of Life. • Long MNA (Mini Nutritional Assessment) for nutritional status.
2.	Phase1: Qualitative Inquiry (Concurrent with quantitative)	Cultural Beliefs and Stakeholder Engagement	• In-Depth Interviews (IDIs), Focus Group Discussions (FGDs), and Key Informant Interviews (KIIs) with leaders, healers, and health workers.
3.	Phase 2: Model Implementation (June – August 2027)	Short-term Model Effectiveness	• Pre-post measures of functional ability and quality of life using the Phase 1 quantitative tools.
4.	Phase2: Evaluation (Sept – Nov 2027)	Feasibility, Acceptability, and Service Utilisation	• Qualitative feedback from participants and stakeholders to refine the model. • Tracking utilisation rates and health screening participation.
5.	Long-Term (18 + months and beyond)	Sustained Improvement and Policy Impact	• Monitoring reduction in functional decline rates and chronic disease complications. • Documenting state-level institutional adoption and policy inputs

**Table 5 pone.0358356.t005:** Data Management Plan outlining data ownership, collection, storage, anonymisation, retention and ethical compliance procedures.

S.NO.	SECTION	DETAILS
1.	Data Ownership	All data generated from this study will be considered the intellectual property of the Department of Community Medicine.
2.	Data Collection	• Data will be collected through questionnaires, informed consent forms, in-depth interviews, focus group discussions, and key informant interviews.• Audio and/or video recordings (where consented) will be transcribed and anonymized.
3.	Data Storage & Access	• Hard Copies:- Questionnaires, consent forms, and field notes will be stored in a locked almirah within the Department of Community Medicine.- The key will remain with the research scholar.• Electronic Data:- Digital files (including transcripts, recordings, and datasets) will be password-protected.- Access will be restricted to the Principal Investigator and the Research Scholar.- Files will be stored on secure institutional computers, with no use of personal devices or unsecured cloud storage.
4.	Data Anonymization	• All participant identifiers will be removed during transcription and data entry.• Pseudonyms or unique ID codes will be used instead of real names.• Publications and reports will not disclose any identifying information.
5.	Data Retention and Disposal	• Data will be maintained until the completion of the PhD work and subsequent publication.• After completion:- Electronic data will be archived securely or deleted as per institutional policy.- Hard copies will be shredded/incinerated or archived according to institutional guidelines.
6.	Ethical Compliance	• The study will follow Institutional Ethics Committee (IEC) guidelines for data confidentiality and participant rights.• Any breach or concern regarding data security will be immediately reported to the Department and IEC.

#### Qualitative component.

The qualitative component will employ convenient sampling to recruit participants with diverse demographic and experiential characteristics. Participants will include middle-aged and elderly tribal community members, frontline health workers, traditional healers, community leaders, Medical Officers, and representatives of local organizations to ensure a broad range of perspectives relevant to healthy ageing and healthcare delivery from five tribal-dominated blocks of East Singhbhum district. The proposed methods and sample distribution for the qualitative component are presented in Table 1.

### Study procedure

#### Phase 1: Concurrent mixed-methods needs assessment.

Phase 1 will focus on conducting a comprehensive needs assessment among middle-aged and elderly tribal populations, in the 5 blocks of East Singhbhum with better operational feasibility.

#### Phase 1 (needs assessment).

Objectives

To assess functional decline and determine prevalent health conditions and risk factors among middle-aged and elderly tribals, in selected blocks of East Singhbhum district.To evaluate the quality of life and associated health determinants, including prevalent risk factors, among the same population groups in the study area.

The quantitative component will employ a community-based cross-sectional design to assess functional status, quality of life, morbidity, nutritional status, and associated risk factors among tribal individuals aged 45 years and above. Following written informed consent, trained investigators will administer a structured interviewer-based questionnaire during household visits. Standardized and validated instruments, including the Barthel Activities of Daily Living (ADL) Index [7], Lawton Instrumental Activities of Daily Living (IADL) Scale [9], WHOQOL-BREF [10] and relevant clinical assessments, will be used to evaluate functional ability, quality of life, nutritional status, and health conditions. Data will be collected from approximately 520 participants selected through a multistage stratified random sampling approach across 25 villages in five tribal-dominated blocks of East Singhbhum district. The findings will identify health needs and priority domains to inform the development of the community-based integrated healthcare model in Phase 2.

The qualitative component will provide contextual and experiential insights into functional decline, healthy ageing, and healthcare needs among tribal populations.

The study will use convenience sampling to capture diverse perspectives across age groups, gender, and social roles.

Participant Groups: Middle-aged (45–59 years) and elderly (≥60 years) tribal individuals, including members of Scheduled Tribes (STs) and Particularly Vulnerable Tribal Groups (PVTGs).Key Informants: KIIs will be conducted with frontline health workers (Sahiyas/ASHAs, ANMs, AWWs), traditional tribal healers, local leaders (Mukhiyas), and Medical Officers to explore cultural practices, healthcare access, and health-system perspectives.FGD Stratification: FGDs will be stratified by age group (45–59 and ≥60 years) and, where feasible, by gender to explore differences in health-seeking behaviour and caregiving experiences.Planned Sample: The qualitative component will include 10 IDIs, 5 FGDs (one per block), and 12 KIIs, with final sample size guided by thematic saturation.

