#### Qualitative component.

For the qualitative inquiry, convenient sampling will be employed to ensure diversity and representation across different age groups, genders, and tribal sub-communities. In-depth Interviews (IDIs), Focus Group Discussions (FGDs), and Key Informant Interviews (KIIs) will be conducted. Key stakeholders will include:

Community members across age categories (middle-aged and elderly).Gender-specific groups to capture differences in health-seeking behaviour and caregiving roles.Community leaders and traditional healers to understand cultural perspectives and indigenous practices related to aging and health.Frontline health workers (ASHA, ANM, AWW’s etc.) Government officials and healthcare providers to explore perspectives on service delivery, challenges, and integration with government programs like NPHCE.

The qualitative tools will explore lived experiences of aging, perceptions of functional decline, caregiving dynamics, health system access, and acceptance of community-based healthcare interventions.

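### With one focus group per block, age (and gender) differences between focus groups cannot be separated from block, and convenience sampling cannot secure the diversity claimed for it

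*Protocol article*

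**What the plan says.** The section on Phase 1 (needs assessment) sets the FGD strata: "FGDs will be stratified by age group (45–59 and ≥60 years) and, where feasible, by gender to explore differences in health-seeking behaviour". Age stratification is stated without condition; gender stratification is conditional.

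The same section fixes the number of sessions: "The qualitative component will include 10 IDIs, 5 FGDs (one per block), and 12 KIIs, with final sample size guided by thematic saturation". The sample size section for the qualitative component gives the same count, "5 Focus Group Discussions (FGDs) (one per block", and so does Table 1. No section says which block is to receive which stratum.

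For the IDIs, the sample size section specifies "one male and one female participant from each of the five study blocks". Their age group is not specified. If new themes emerge, "additional interviews (up to 20% of the proposed sample) may be conducted after notification to the Institutional Ethics Committee (IEC".

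On recruitment, the data collection method section says that "convenient sampling will be employed to ensure diversity and representation across different age groups, genders, and tribal sub-communities". The sampling strategy section and the Phase 1 section make similar claims for the method, and the sample size section expects the sample to represent gender, age and stakeholder groups adequately.

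**The concern.** Two statements about the FGDs pull against each other. One asks them to show how age groups, and possibly men and women, differ in health-seeking and caregiving. The other places a single FGD in each block. The study setting section explains that the five blocks were taken to cover the geographical, socio-cultural and healthcare diversity of the district, and the qualitative analysis plan counts coverage of five blocks as a way to capture varied experience. The same five sessions must therefore show block variation and age variation at once, with nothing in the layout to tell them apart.

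The second issue is what the sampling method is said to deliver. Convenience sampling takes those who are accessible. It may happen to produce a varied group, but it does not ensure one. Apart from gender within block for the IDIs, no quota is stated for age, Scheduled Tribe (ST) or Particularly Vulnerable Tribal Group (PVTG) membership, or functional limitation.

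At stake is interpretation in Phase 2. The section on model refinement reads survey patterns by gender alongside qualitative insight into caregiving and health-seeking, which are the FGD topics. A block feature, or a feature of who was easy to recruit, could be taken for a need of an age or gender group and written into the model.

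**Working it through.** **Inputs.** Five blocks (study setting); one FGD per block (sample size section, Table 1, Phase 1 section); two age groups, and two genders where feasible (Phase 1 section); one man and one woman interviewed per block (sample size section); a reserve of up to 20% (same section).

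**The plan's own counts.** FGDs: 1 × 5 = 5. IDIs: 2 × 5 = 10. With 12 key informant interviews the total is 10 + 5 + 12 = 27. These reproduce.

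**FGDs by age.** Five sessions in five blocks mean that the five block indicators already account for all five sessions. Adding an age indicator leaves the rank of the design at 5 for every possible allocation of age to block. Age is therefore fully aliased with block. The most even split is 3 blocks against 2. The same holds for gender if groups are single-gender.

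**FGDs by age and gender.** Five groups can be spread over the four age-by-gender cells in 4^5 = 1,024 ways. Of these, C(5,2) × 4! = 10 × 24 = 240 cover all four cells, always as 2-1-1-1. Three of the four cells then rest on one group from one block, so saturation within a stratum cannot be judged.

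**What separation would need.** Both age groups in every block: 2 × 5 = 10 FGDs.

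**The reserve.** Applied to FGDs alone, 20% of 5 = 1. Six FGDs would let one block hold both age groups (rank 6). Applied to all sessions, 20% of 27 = 5.4, or five sessions. If all five were FGDs, the total would reach 10. However, the text speaks of interviews and ties them to the emergence of new themes, not to balancing strata.

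**IDIs by gender.** Five block indicators plus gender have rank 6, so gender is crossed with block and not mixed with it. Age is left open.

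**Check of the proposed IDI layout.** Call a block type A if it pairs a man aged 45–59 with a woman aged ≥60, and type B if it pairs a man aged ≥60 with a woman aged 45–59. Let dA and dB be the woman-minus-man difference within each type. Block effects cancel within each difference.

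- Gender contrast, averaged over age: (dA + dB)/2.
- Age contrast (older minus younger), averaged over gender: (dA − dB)/2.
- The age-by-gender interaction equals the sum of the two people in A blocks minus the sum in B blocks, so it remains mixed with block.

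With three A blocks and two B blocks, each age group has 3 + 2 = 5 interviewees.

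**The case against.** The strongest reply is that a qualitative strand should not be judged as a factorial experiment. No test or estimate is planned from the FGDs, the aim is to explore, and the protocol nowhere plans to cross age, gender and block. That stands. The layout argument shows only what cannot be attributed, not that the FGDs lack value.

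Several stronger readings are tempting and the documents do not support them.

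- A reader might infer that five FGDs cannot be stratified at all. They can, as 3/2 by age or 2-1-1-1 by age and gender. The defect is lack of replication and confounding with block.
- A reader might infer that all qualitative age and gender contrasts are mixed with block. This is untrue of gender in the IDIs. IDI age is unspecified, so both age groups might also be heard in a block through the interviews.
- A reader might infer that the gender-stratified model rests on these contrasts. The section on Step 2 of model development bases it on questionnaire findings, and the section on model refinement adds qualitative insight as context. Comparisons across age categories and gender-stratified analyses sit in the quantitative plan.
- A reader might infer that convenience sampling will miss remote or functionally limited people. That is plausible, but the protocol does not say how people will be approached, and the study population is all eligible tribal adults aged 45 and over.

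It may also be said that the alternating IDI pairing recreates the problem. It does so for the interaction, but not for the two main contrasts.

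**Conclusion.** The point holds in limited form. Age differences between FGDs are completely confounded with block, and so are gender differences if groups are single-gender. At best three blocks stand against two. This assumes that stratifying means each FGD is drawn from one age group and that the count stays at one per block; a sixth FGD would relieve it in one block only. The claim that convenience sampling ensures diversity and representation is wrong as stated, whatever sample it happens to produce.

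The consequence is moderate. The contrasts are exploratory and complement the survey of 520, whose sample size and analyses are untouched. The change should still be made, because the wording invites an attribution that the layout cannot support and the remedy is cheap.

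**What to change.** Keep the same number of sessions and make three changes.

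1. Replace convenience sampling of community members with purposive maximum-variation sampling from the household listing described under the data collection procedure. Set quotas for age group, gender, ST/PVTG status and functional limitation, and make the wording consistent in every section that names the method.
2. State that FGD differences by age or gender are descriptive and cannot be separated from block, and record which stratum each block received.
3. Fix age as well as gender in the ten IDIs: a man aged 45–59 with a woman aged ≥60 in one block, the reverse in the next, alternating across the five blocks. Note that the age and gender main contrasts are then each separable from block, but their interaction is not.

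The cost is revised wording, a recruitment grid and slightly more effort than taking whoever is available. The listing is described as identifying people by age, so functional limitation would need a short added question or would have to be taken from survey interviews as they are completed. The protocol gives 15 May 2026 as the start of recruitment. If any sessions have already been held, their age and gender composition should be recorded and the grid applied to the rest.

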
#### Phase 2: Development of the community -based healthcare model.

Objective 3. To design a community-based, culturally sensitive healthcare model to assess its feasibility and acceptability in improving functional ability and Quality of life across middle-aged and elderly tribal populations across all the blocks of East Singhbhum.

Phase 2 will build on the integrated quantitative and qualitative findings from Phase 1 to fulfil Objective 3, which involves developing a culturally appropriate, community-based integrated healthcare model for healthy aging among tribal populations. The identified domains from Phase 1 will be refined through stakeholder consultations involving tribal community representatives, Medical Officers, traditional healers, local leaders, public health experts, and other relevant stakeholders. Support from ASHA/Sahiya workers and local community stakeholders will be sought throughout participant mobilisation, community engagement, and implementation of the healthcare model Fig 3. Based on the consensus generated, the healthcare model will be developed and implemented in a selected village to assess its effectiveness, feasibility, and community acceptability. Written informed consent will be obtained from all participants prior to their involvement, either through signature or thumb impression.

